### Data management

#### REDCap

Data collection and site-level management are conducted using REDCap, a browser-based metadata-driven software system (Vanderbilt University, Nashville, TN, USA) [39]. Most study instruments, including the recruitment log, online surveys, and laboratory results, allow for real-time data entry directly into REDCap. Surveys are designed to be self-administered electronically through the Internet using home computers, personal mobile telephones, or on computers or tablets provided at the workplace by study staff. In addition, study staff enter participants’ responses directly into the REDCap database for interviews administered by telephone. Routine quality assurance monitoring is conducted locally by the project manager and centrally by the data coordinator (Abt Associates). Missing or unclear information is corrected through follow-up contact with participants.

#### TextIt

TextIt (TextIt, Kigali, Rwanda) is an online platform that uses logic flows to send tailored SMS messages to participants. Custom decision trees were developed in order to trigger exchanges with participants during active surveillance (described above). Specifically, TextIt documents answers to weekly illness inquiries, dates of illness onset and resolution, ratings of symptoms, and missed work. Study staff perform bi-weekly exports of TextIt data and import the data into an Excel macro-enabled workbook in order to track participant responses and illness events over time (see Additional file 1: Annex 6 for more details about TextIt).

### Statistical considerations

#### Cohort size

The required number of participants depends on multiple factors, including expected influenza attack rate, vaccination coverage, and anticipated study attrition. We estimated that with 2340 participants contributing 5 months at-risk for influenza infection per season, 40% vaccine coverage, and 10% influenza illness attack rate, we would be powered to estimate a true vaccine effectiveness of 50% with confidence intervals that do not overlap with zero.

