Although recent reviews confirm that the seasonal influenza vaccine is moderately effective in reducing the risk of influenza illness among adults [18], multiple gaps in knowledge remain about the preventive value of the vaccine among HCP [1]. To date, there has been only one randomized controlled trial of influenza vaccine efficacy among HCP, and this study measured serologic outcomes only [19]. Given that vaccinated individuals are less likely to seroconvert after an influenza virus infection and so can appear as not having been infected [20, 21], the use of serologic outcomes likely biases (and specifically, inflates) vaccine efficacy estimates.

Gaps are especially evident in our understanding of the value of influenza vaccine for reducing secondary adverse outcomes, including nosocomial infections among patients [22, 23] and missed work due to illness [24, 25]. Evidence is also needed to validate the potential of the vaccine in reducing the severity and duration of disease and diminish infectiousness among those who have breakthrough infections despite being vaccinated [24, 26]. Because HCP often receive influenza vaccine during multiple years, studies of HCP also provide an opportunity to examine how prior vaccinations may modify immunogenicity and vaccine effectiveness, and may provide answers to questions regarding the extent of residual protection and/or negative vaccine interference across seasons [27–29].

Here we provide an overview of the design and methods of a prospective study of influenza vaccine effectiveness in HCP named “Study of Healthcare Personnel with Influenza and other Respiratory Viruses in Israel” (SHIRI). The SHIRI cohort will follow approximately 600 HCP, all of whom have direct patient contact, during at least three influenza seasons, and an additional 1400 HCP during at least two influenza seasons.

Our study has four primary objectives: (1) to describe the frequency of respiratory, atypical (e.g., febrile only), and asymptomatic influenza virus infection among HCP; (2) to identify predictors of vaccine acceptance (and hesitancy) among HCP; (3) to examine how repeated influenza vaccination may modify immunogenicity; and (4) to evaluate influenza vaccine effectiveness in preventing influenza illness, associated missed work, and working while ill. Table 1 lists the knowledge gaps we identified within each of these aims and the study features intended to address these gaps.

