#### Timeline of enrollment

A total cohort of 2000 HCP will be enrolled over a three-year period. Enrollment periods are targeted prior to influenza seasons. During Year 1 of the study, which targeted the 2016/2017 influenza season, enrollment could not begin until October 6, 2016 due to funding and institutional approval delays. Recruitment continued until the start of the influenza season (December 4, 2016) for a total of 8 weeks. This recruitment period included a month of frequent Israeli national holidays (October 2016), during which enrollment was challenging because many HCP were on vacation. In Year 1 of the study, 596 HCP were enrolled, and will contribute to Years 1, 2 and 3 of this 3-year cohort study. Enrollment in Year 2 began in June 2017. New enrollees in Year 2 will contribute to Years 2 and 3 of the study.

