**Fig. 2 Fig2:**
[figure not shown]
Active Surveillance SMS Messaging Flow

The start and end of active surveillance is determined by the study investigators and steering committee based on historical patterns for seasonal influenza circulation and available clinical and surveillance indicators of laboratory-confirmed influenza virus circulation in Israel. In the first year of the study, active surveillance started on December 4, 2016 and continued through March 23, 2017.

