## Discussion

We described the recruitment, enrollment, active surveillance, data collection, laboratory methods, and data management procedures for the SHIRI cohort – a US CDC-sponsored prospective study, overseen by CHS, of approximately 2300 HCP at two hospitals in Israel. In this study, we will describe the frequency of influenza virus infections among HCP in Israel. Using a broad case definition of respiratory illness, we aim to identify a wide range of ARFI in order to assess more accurately the burden of respiratory illness among HCP. Due to CHS’s extensive EMR, we will have the ability to look at HCP influenza vaccination records up to 10 years prior to study enrollment in order to better understand how HI antibody titers differ depending on the number and specific combinations of prior influenza vaccinations. We will also be able to evaluate influenza vaccine effectiveness in preventing medically attended and non-medically attended influenza illness and associated missed work days.

The findings from the SHIRI cohort will increase our understanding of the burden of acute respiratory illnesses, and influenza virus illness specifically, among HCP in Israel. The unique design of the study, which includes comprehensive medical and vaccination data, active surveillance using a broad case definition, and both molecular and serologic diagnostics, will provide important data on influenza vaccine immunogenicity and effectiveness among HCP. The combination of insights about influenza burden and vaccine effectiveness may potentially inform influenza vaccine policy for HCP in Israel and internationally.

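### The numeric sample-size basis for vaccine effectiveness (2340 participants, 5 months per season) does not match the planned cohort of 2000 or the surveillance season as run

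*Protocol article*

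**What the plan says.** The Cohort size section is the only place that gives numbers for the VE sample size. It assumes "2340 participants contributing 5 months at-risk for influenza infection per season, 40% vaccine coverage, and 10% influenza illness attack rate" and concludes that a true VE of 50% could be estimated with a confidence interval that excludes zero. The two neighbouring subsections, on incidence and on immune response, give no VE assumptions.

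The size of the cohort is stated differently elsewhere:

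- Timeline of enrollment: "A total cohort of 2000 HCP will be enrolled over a three-year period". It also reports that 596 were enrolled in Year 1.
- Background: "The SHIRI cohort will follow approximately 600 HCP" for at least three seasons, plus a further 1400 for at least two, which again makes 2000. The abstract also says about 2000.
- Discussion: a study "of approximately 2300 HCP at two hospitals in Israel".

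On exposure, the Active surveillance section reports that in the first year "active surveillance started on December 4, 2016 and continued through March 23, 2017". The VE analysis section uses weeks of active surveillance as the person-time denominator, so this window is the quantity that the 5 months should correspond to.

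**The concern.** The article prints a calculation for a cohort that it does not plan to enrol. Attrition cannot explain the gap. The calculation has 2340 people contributing time at risk, so enrolment would have to be above 2340, yet planned enrolment is 2000. Nor is 2340 the number of planned person-seasons, which is about 4,590. The assumed season is also longer than the only one observed.

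What is at stake is whether a reader can tell what precision the design offers. The section does not say whether the claim is for one season or for all seasons pooled, or whether the 10% attack rate is overall or among the unvaccinated. Each choice changes the expected interval.

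**Working it through.** **Inputs.** From Cohort size: N = 2340, 5 months, coverage 40%, attack rate 10%, VE 50% (rate ratio 0.5). From Timeline of enrollment and Background: 2000 HCP, of whom 596 started in Year 1. From the VE analysis section: 95% intervals. Assumptions made here: unadjusted rate ratio, no attrition, independent person-seasons.

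**Size and exposure.**

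- Shortfall in cohort: 1 − 2000/2340 = 14.5%. The Discussion's 2300 is 1.7% below 2340.
- Year 1 window, both end dates included: 28 + 31 + 28 + 23 = 110 days; 110/30.4375 = 3.6 months; 3.6/5 = 72%.
- Person-months in one season: 2340 × 5 = 11,700 against 2000 × 3.6 = 7,200, which is 38% fewer.
- Planned person-seasons: 596 × 3 + 1404 × 2 = 4,596 (4,588 with the rounded 1400).

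**Formulas, reading 10% as the overall rate.** The unvaccinated rate is 0.10/(1 − 0.4 × 0.5) = 0.125 and the vaccinated rate is 0.0625. Expected cases are 0.4 × 0.0625 × N = 0.025N vaccinated and 0.6 × 0.125 × N = 0.075N unvaccinated. SE(log RR) = √(1/cases_v + 1/cases_u). The VE limits are 1 − 0.5 × exp(±1.96 × SE). Power is Φ(0.693/SE − 1.96).

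| Case | Cases (vacc., unvacc.) | SE | Expected 95% CI for VE | Power |
|---|---|---|---|---|
| 2340, one season (the plan's figure) | 58.5, 175.5 | 0.151 | 33–63% | 99.6% |
| 2000, one season | 50, 150 | 0.163 | 31–64% | 98.9% |
| 2000, cases × 0.72 | 36, 108 | 0.192 | 27–66% | 95.0% |
| 4,596 person-seasons pooled | 114.9, 344.7 | 0.108 | 38–60% | >99% |

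The first row reproduces the plan's own claim: with its inputs, the interval does exclude zero with high probability.

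**Reading 10% as the unvaccinated rate.** Expected cases become 0.02N and 0.06N. Power is 98.4% at 2340, 96.7% at 2000 (lower limit 28.5%), and 89.6% at 2000 with cases scaled by 0.72 (lower limit 23.8%). Pooled power stays above 99%, with or without scaling. A two-proportion comparison gives slightly higher power in each single-season case (for example 98.7% at 2000, and 93.6% after scaling).

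**Year 1 alone, as a caution.** With 596 HCP and a 10% overall rate, the expected cases are 14.9 and 44.7, SE is 0.299, the interval is about 10–72% and power is 64%. Across both readings of the 10%, with and without scaling, and by either method, power runs from about 42% to 71%.

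**The case against.** The strongest reply is that the mismatch hardly matters. Going from 2340 to 2000 moves one-season power from 99.6% to 98.9%, and the pooled analysis has ample precision. That stands, and it limits the point to a wrong stated basis.

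The season-length element is also open to challenge. Five months is a planning assumption and 3.6 months is one realised season. Later windows are set each year from circulation data, and a seasonal attack rate need not fall in proportion to the window if it covers most of the circulation. This stands too, so the scaled figures are a worst case and not a forecast.

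Three stronger readings are tempting, and the document does not support them:

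- A reader might infer that 2340 does not follow from its inputs, because conventional power levels need far fewer people (for example 927 for 80% and 1,225 for 90% with 10% against 5%). But no power level is stated and 2340 is not called a minimum, so there is nothing for it to fail to follow from.
- A reader might infer that each season, including Year 1 with 596 HCP, is claimed to be powered. In the text, per season qualifies the months at risk and not the confidence interval. The VE model includes study year, which points towards analysis across years, and no section says that Year 1 alone is powered.
- A reader might fault the absence of attrition and power values. A condensed article may leave these to the full protocol or analysis plan.

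The inconsistency itself remains. The article chose to print a numeric basis, and that basis conflicts with its own enrolment plan and its own surveillance dates. The Discussion's 2300 lies close to 2340 but contradicts the 2000 given in three other places.

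**Conclusion.** The point holds as an inconsistency in the stated basis and not as a loss of power. The calculation assumes 14.5% more people than the plan enrols and a season about 39% longer than the one observed (5/3.6 = 1.39). On the planned 2000 HCP, the conclusion that the interval excludes zero at a true VE of 50% still stands. One-season power is about 90 to 99% by the rate-ratio method, depending on how the 10% is read and whether cases scale with the window. Pooled power is above 99%. Precision is slightly less favourable than 2340 would suggest.

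These results are unadjusted. They take no account of attrition, repeated seasons in the same person or the propensity-score adjustment. The Year 1 range of about 42 to 71% is only a warning against reading the claim as applying to every season separately.

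**What to change.** 1. Use one cohort size in the abstract, Background, Timeline of enrollment, Cohort size and Discussion. If 2340 or 2300 is a later target, say so and change the 2000; otherwise correct the other two.
2. Restate the Cohort size calculation on the planned 2000 HCP and the planned person-seasons (596 in Year 1, then about 2000 in each of Years 2 and 3, so about 4,590 before attrition).
3. Use a season length consistent with surveillance as run, or explain why 5 months is expected in later seasons.
4. Say whether the 10% attack rate is overall or among the unvaccinated, and whether the claim is for one season or pooled. Give the expected interval for the case meant.
5. Optionally, add a sentence that a Year 1 estimate on its own will be imprecise.

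The cost is a short recalculation and wording changes. The stated one-season precision becomes slightly less favourable. No extra enrolment or change of design is needed.

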#### Sample size for incidence calculations

The full cohort provides the sample needs for estimating the frequency (or incidence within the study sample) of influenza illness. Given the larger sample demands for the vaccine effectiveness objectives, we expect to have ample statistical power for most objectives that involve estimating incidence or frequencies.

#### Sample size for immune response to vaccine and infection objectives

To assess the immune response to the vaccine, we plan to collect serum from the cohort members prior to vaccine availability, after vaccination, and at the end of each season. Our study design mirrors approaches used in previous studies that assessed the HI antibody titers among HCP analyzed sera from subgroups of 300–800 participants who provided sera at the same three time points [28]. See Additional file 1: Annex 7 for more details.

#### Data analysis of VE

Rates of acute illness associated with mqRT-PCR confirmed influenza virus infection (influenza illness) will be calculated as the number of influenza illnesses divided by person-time measured in weeks of active surveillance. Regression models will be used to estimate influenza vaccine effectiveness (1 – rate of influenza illness among vaccinated HCP/rate among unvaccinated HCP * 100) with 95% confidence intervals. Adjusted models of influenza vaccine effectiveness will include study year, calendar time (i.e., weeks between illness onset and week of peak of influenza season), and a propensity for vaccination score calculated using multivariable logistic regression [40]. Other potential confounders, including study site, will be examined and included in the adjusted model if they change IVE point estimates by > 5%.

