### Active surveillance

During the influenza season, participants receive twice-weekly short message service (SMS) messages asking them to confirm whether they have acute illness symptoms, defined as one or more of the following symptoms within the past 7 days: cough, runny nose, body aches, or feverishness. In addition to these SMS messages, participants are asked to contact the study staff immediately when they experience symptoms of acute illness. If a participant reports an acute illness, he or she is asked follow-up questions about specific symptoms and date of onset. Participants are first contacted by SMS message. If they do not respond, they are contacted by telephone. If participants do not respond to phone calls, an attempt is made to contact them in-person. Ill participants receive follow-up SMS messages about whether the illness has resolved. Once an illness resolution is reported by a participant, he or she is sent five follow-up questions by SMS message about illness presentation, duration, and impact on work attendance. These surveillance activities are described in Fig. 2.

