### Laboratory methods

#### Nasal specimens

When participating HCP report being ill with a respiratory illness during the influenza season, they are instructed to self-collect a nasal swab using a self-swabbing kit [31] that includes illustrated instructions, a nasal mid-turbinate swab, and a tube with room temperature transport medium. Respiratory specimens are placed in viral transport medium and delivered to the respective hospitals from HCP’s residences by a courier service or are hand-carried by participants to study staff at their respective hospitals. If participants prefer not to collect the nasal swab themselves, study staff are able to collect it for them.

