### Strengths

Our study benefits from the fact that all enrolled HCP are members of CHS, and therefore extensive information is recorded in the EMR, which provides real-time data about ambulatory visits, hospitalizations, and medication use. In addition, the EMR provides reliable historic data about the participants, such as prior vaccination information, socio-economic variables, and data about health status and health behaviors. In our study, even if an ARFI is not reported through the SMS surveillance system, daily monitoring of the EMR for medical visits and medications will allow us to identify illnesses and contact participants directly in order to collect respiratory specimens and complete the illness survey. Combining our study with EMR data and data from the two hospitals’ human resources departments will also allow us to reliably map the impact of illness on missed work and to evaluate days worked when ill (presenteeism).

In addition, the broad case definition of an ARFI promises to be more sensitive for influenza illness than case definitions used in previous HCP research [24] and should allow us to characterize a continuum of mild to moderately severe illnesses. Another strength is that the two study sites (Soroka University Medical Center and Beilinson Hospital) are among the largest hospitals in Israel, and the populations they serve and the HCP they employ vary in socio-demographic and economic characteristics. Soroka University Medical Center, the only general hospital in the Negev region in southern Israel, serves two main local populations: Jews, who mostly live in urban settings, and Bedouin Arabs, who live in a range of settlement types, from cities to unrecognized rural villages that lack electricity and running water [42, 43]. Beilinson Hospital, located in central Israel, serves a mostly urban population of a relatively higher socio-economic status compared to Soroka University Medical Center. Conducting our study in these two different settings may allow us to identify socio-demographic differences in KAP, vaccine uptake, and influenza illness attack rates. The use of mixed methods, including laboratory, clinical and epidemiological quantitative data, and in-depth qualitative interviews, creates a comprehensive approach, which is particularly important when trying to understand issues of influenza vaccine compliance and hesitancy. Finally, the study cohort includes several unique sub-studies.

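### The influenza illness rate treats an unswabbed illness as a non-case, so incidence is understated to the extent that true cases go unswabbed, and VE is biased if swabbing differs by vaccination after adjustment

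*Protocol article*

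**What the plan says.** Data analysis of VE fixes both parts of the rate. The outcome is confirmed disease only ("Rates of acute illness associated with mqRT-PCR confirmed influenza virus infection (influenza illness"), and the rate is the "number of influenza illnesses divided by person-time measured in weeks of active surveillance". VE is then "1 – rate of influenza illness among vaccinated HCP/rate among unvaccinated HCP * 100". The adjusted models include study year, calendar time and a vaccination propensity score. Other confounders enter if they move the VE estimate by more than 5%. No term for response or swabbing is named.

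A case has to pass through surveillance and then a swab. Under Active surveillance, "participants receive twice-weekly short message service (SMS) messages asking them to confirm whether they have acute illness symptoms", with a 7-day symptom look-back. The same section describes telephone follow-up of non-responders, and then: "If participants do not respond to phone calls, an attempt is made to contact them in-person". Under Nasal specimens, when participants report a respiratory illness "they are instructed to self-collect a nasal swab using a self-swabbing kit", and staff can take the swab for those who prefer that. Under Strengths, "daily monitoring of the EMR for medical visits and medications will allow us to identify illnesses", with direct contact to obtain a specimen.

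Active surveillance is also described as a calendar window. In Year 1, "active surveillance started on December 4, 2016 and continued through March 23, 2017".

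**The concern.** A confirmed-case numerator over surveillance time measures the influenza illness rate multiplied by the probability that an illness is captured. An ARFI episode that ends without a valid swab has unknown influenza status, but the formula gives it the same weight as a proven negative.

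Two objectives are exposed. Objective 1 (frequency of influenza) loses the unswabbed true cases. Objective 4 (VE) is shifted by the ratio of capture in vaccinated to capture in unvaccinated HCP, where that ratio departs from 1 after adjustment.

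The article gives reasons why capture could differ, and they point in opposite directions. Vaccinated participants are asked for an extra blood draw (Blood Specimens), and blood draws earn small gifts (Ethical considerations), so they may be more engaged. On the other hand, Table 1 asks whether vaccination makes breakthrough illness milder and shorter, and milder illness may be swabbed less often. The Background criticises serologic endpoints because detection differs by vaccination status, which is the same kind of error.

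**Working it through.** **Inputs from the documents.** Cohort size gives 2340 participants, 40% vaccine coverage, a 10% attack rate and true VE 50%. Data analysis of VE gives the rate and the VE formula. No response or swabbing fraction is given anywhere, so the plan has no figure of its own to reproduce here and every capture value below is an assumption.

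**Formulas.** Let s_v and s_u be the probabilities that a true influenza illness in vaccinated and unvaccinated HCP ends in a valid swab. Person-time is unaffected by a missing swab, so:

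- observed rate = true rate × s in each group
- observed VE = 1 − (1 − true VE) × s_v / s_u
- observed attack rate = 0.4 × AR_v × s_v + 0.6 × AR_u × s_u

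Reading the 10% as the overall attack rate, AR_u = 0.10 / (1 − 0.4 × 0.5) = 12.5% and AR_v = 6.25%.

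**Results with true VE 50% and true attack rate 10%.**

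| s_v / s_u (assumed) | Observed VE | Observed attack rate |
|---|---|---|
| 80% / 80% | 1 − 0.5 × 1 = 50% | 8.0% |
| 90% / 80% | 1 − 0.5 × 0.90/0.80 = 44% | 8.3% |
| 80% / 90% | 1 − 0.5 × 0.80/0.90 = 56% | 8.8% |
| 90% / 70% | 1 − 0.5 × 0.90/0.70 = 36% | 7.5% |
| 70% / 90% | 1 − 0.5 × 0.70/0.90 = 61% | 8.5% |

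These are crude ratios. They apply to the capture gap left after adjustment.

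**Scale.** For one season of 2340 participants, expected cases are 0.6 × 2340 × 0.125 = 175.5 unvaccinated and 0.4 × 2340 × 0.0625 = 58.5 vaccinated. The standard error of the log rate ratio is √(1/175.5 + 1/58.5) = 0.151, so the 95% interval around VE 50% runs from about 33% to 63%. A 10-point residual gap in capture (shift about 6 points) lies well within that interval. A 20-point gap (shift 11 to 14 points) is close to its half-width.

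**The unanswered-week question.** Suppose response is 90% in vaccinated and 75% in unvaccinated HCP, with swabbing equal at 80%. If all calendar weeks count, observed VE = 1 − 0.5 × (0.90 × 0.80)/(0.75 × 0.80) = 40%. If only answered weeks count, it is 50%. If swabbing is also 90% against 75%, the two figures are 1 − 0.5 × 0.81/0.5625 = 28% and 1 − 0.5 × 0.90/0.75 = 40%. Restricting person-time then does not suffice. The swabbing correction is needed as well, and it returns 50% only if swabbing is missing at random.

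**The case against.** The strongest reply is that handling of missing swabs and unanswered messages normally belongs in an analysis plan, and a condensed article need not carry it. For unanswered weeks this stands. A reader might infer that every unanswered week is counted as influenza-free, because active surveillance has calendar start and end dates. The text does not say so, and weeks actually surveilled is an ordinary reading of the same words. For unswabbed illnesses the reply does not stand, because the written formula already determines how they enter.

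The safeguards are substantial: twice-weekly contact with a 7-day look-back, escalation to telephone and in person, staff swabbing, and EMR monitoring that triggers specimen collection. They reduce the loss without removing it. EMR monitoring reaches only illness that led to a visit or medication. The end-of-season survey asks about unreported illness, but no swab is described for it. Serologic detection of infection is planned only for unvaccinated HCP (Table 1).

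A reader might also infer that the attack rate is always understated. It is understated only if true influenza illnesses are missed, and Objective 1 also draws on serology in unvaccinated HCP, so this ratio is not its only measure.

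Nor is it right that propensity adjustment cannot help. Capture differences that run wholly through covariates in the score are balanced by it; only the residual difference biases VE.

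Finally, no document figure shows that swabbing differs by vaccination status, and the direction is unknown. That also stands.

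**Conclusion.** The point holds for unswabbed illnesses. Under the stated formula they add person-time and cannot be cases, so the rate is understated in proportion to the true influenza illnesses that go unswabbed. VE is biased upwards or downwards only if swabbing differs by vaccination status after adjustment. The illustration is a move from 50% to 44% or 56% for a 10-point residual gap, and from a 10% to an 8% attack rate at 80% capture in both groups. It rests on assumed capture values and on the article's planning values. The documents do not support a claim that VE will be biased in a known direction. The denominator is ambiguous for unanswered weeks and should be clarified; it is not a stated error. This is worth correcting because the remedy is cheap and rests largely on data already collected.

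**What to change.** In Data analysis of VE:

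1. Treat an ARFI episode without a valid swab as having unknown influenza status. Add a pre-specified analysis of VE and incidence that either weights swabbed episodes by the inverse probability of being swabbed, given vaccination status, site, calendar week, symptoms and occupation, or multiply imputes influenza status. Report it beside the confirmed rate as now written, and state the missing-at-random assumption.
2. Report surveillance response and swab proportions by vaccination status.
3. State that person-time is the weeks whose illness status is known from routine surveillance answers. Handle weeks known only through EMR-triggered contact in a sensitivity analysis. Otherwise a non-responder's week would count because that person was ill and sought care, while their healthy unanswered weeks dropped out, and person-time would depend on the outcome.

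Cost: some added wording and a little more analysis work. Responses and symptoms are logged in TextIt, laboratory results in REDCap, and vaccination in the EMR. Intervals will be slightly wider.

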## Methods/design

### Study design

This prospective cohort study of influenza vaccine effectiveness in HCP is funded by the United States Centers for Disease Control and Prevention (US CDC). A steering committee, consisting of principal investigators from the two hospitals, Clalit Health Services (CHS), the Israeli Center for Disease Control, Abt Associates, and the US CDC was established and charged with making critical decisions related to the study. Additional investigators from the University of Michigan School of Public Health and the Ben Gurion University School of Public Health will advise on laboratory methods and qualitative methods related to the study. Study activities are described in Fig. 1.

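### The adjusted VE model requires a calendar-time covariate measured from illness onset, which participants and person-weeks without illness do not have

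*Protocol article*

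**What the plan says.** All of the model text is in the Protocol article, Statistical considerations, Data analysis of VE.

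- The rate is the "number of influenza illnesses divided by person-time measured in weeks of active surveillance".
- VE comes from regression models as "1 – rate of influenza illness among vaccinated HCP/rate among unvaccinated HCP * 100", reported "with 95% confidence intervals".
- "Adjusted models of influenza vaccine effectiveness will include study year, calendar time" and a vaccination propensity score. These terms are fixed. Study site and other candidates enter only if they move the VE estimate by more than 5%.
- Calendar time is spelled out as "calendar time (i.e., weeks between illness onset and week of peak of influenza season".

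Two other sections bear on this. Active surveillance says where an onset date comes from: "If a participant reports an acute illness, he or she is asked follow-up questions about specific symptoms and date of onset". Study design describes the work as "This prospective cohort study of influenza vaccine effectiveness in HCP". No section describes a test-negative or case-only VE analysis.

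**The concern.** The rate ratio compares vaccinated and unvaccinated person-time, and that person-time includes every week in which nobody fell ill. A covariate counted from illness onset has no value in those weeks. The denominator and the mandatory covariate therefore cannot both be used as written.

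Calendar time is worth adjusting for. The article counts vaccination from 1 September to 31 March, and Year 1 surveillance ran from 4 December to 23 March, so some vaccination can fall inside follow-up. Vaccinated and unvaccinated weeks should then be compared at the same level of virus circulation. A term that is empty for illness-free weeks cannot do this.

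VE against influenza illness is part of the fourth of the article's primary objectives, and this is the only adjusted VE model it describes. Two analysts following the sentence in good faith could report quite different VE estimates.

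**Working it through.** **The plan's own figure.** Cohort size works "with 2340 participants contributing 5 months at-risk for influenza infection per season", with 40% coverage, a 10% attack rate and VE 50%. If 10% is the risk in the unvaccinated:

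- Expected cases: 2340 × 0.6 × 0.10 = 140.4 unvaccinated and 2340 × 0.4 × 0.05 = 46.8 vaccinated, 187.2 in all.
- SE(log rate ratio) = √(1/140.4 + 1/46.8) = 0.169.
- 95% CI for the ratio: 0.5 × exp(±1.96 × 0.169) = 0.36 to 0.70, so VE 30% to 64%.

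The statement that the interval excludes zero holds for a comparison over the whole cohort. The number 2340 itself cannot be derived, because no power is stated. The point here does not depend on it.

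**Simulation.** 300 cohorts of 2340; 40% vaccinated; season risk 10% unvaccinated and 5% vaccinated (true VE 50%). Assumed, not in the article: 16 surveillance weeks (close to Year 1), a bell-shaped epidemic peaking at week 8, and non-influenza illness in 40% of those without influenza. The covariate is the absolute distance in weeks from the peak. Models are Poisson with a log person-time offset, except the logistic row.

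| How calendar time is handled | Median VE | 2.5th to 97.5th percentile |
|---|---|---|
| No calendar term | 51% | 34% to 68% |
| Distance of each person-week from the peak, whole cohort | 51% | 34% to 68% |
| As written, influenza cases only (about 188 people) | -1% | -12% to 9% |
| As written, non-cases set to 0 weeks | 36% | 9% to 63% |
| As written, non-cases set to their last surveillance week | 13% | -10% to 30% |
| Logistic, all ill participants (about 1050 people), odds ratio | 53% | 33% to 71% |

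**Why the rows come out this way.**

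- *Whole cohort, 51%.* The 50% was set as a ratio of season risks. Cases stop contributing time at onset, near week 8 on average, so mean follow-up is 0.05 × 8 + 0.95 × 16 = 15.6 weeks in the vaccinated and 0.10 × 8 + 0.90 × 16 = 15.2 in the unvaccinated. The rate ratio is 0.5 × 15.2/15.6 = 0.487, so VE is 51.3%.
- *Cases only.* Every record is an event, so the fit compares only how early cases occurred. Attack rates have dropped out, and VE sits near zero.
- *Filled-in values.* With 0 for non-cases, any non-zero value marks a case. With the last week (distance 16 - 8 = 8), any value below 8 marks a case. The covariate then carries part of the outcome and absorbs part of the vaccine effect.
- *All ill participants.* Non-influenza illness is 0.4 × 0.95 = 0.38 in the vaccinated and 0.4 × 0.90 = 0.36 in the unvaccinated. The odds ratio is (0.05/0.38)/(0.10/0.36) = 0.474, so VE is about 53%. This is close to the truth, but it is an odds ratio among the ill and not a rate ratio over person-weeks.

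**The case against.** The best defence is that the named covariate is calendar time and the words after it only describe its scale. Distance from the peak is defined for every surveillance week, the denominator is already in person-weeks, and that reading recovers VE. A condensed article may also leave model form and time-splitting to an analysis plan that is not shown. Part of this stands: the authors may well have meant it. But the text states a definition, counts from illness onset, makes the term mandatory, and is not redefined elsewhere. That is a stated rule that does not fit the stated denominator, not a missing detail.

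Three stronger readings are tempting, and the document supports none of them.

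- A reader might infer that VE must be biased. It need not be. Among all ill participants, if the non-influenza illness risk n is the same in both groups, the odds ratio is (0.05/n)/(0.10/n) = 0.50 for any n, so VE is 50%. A ratio of influenza-positive proportions among the ill would be attenuated, but the article describes no such analysis.
- A reader might infer that the fit necessarily conditions on influenza. The covariate refers to illness onset, and any reported acute illness has one. Restricting to people with an onset conditions on illness.
- A reader might infer that the primary model is broken. The article calls the objective primary and names no primary model.

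**Conclusion.** The point holds as a defect of definition. The mandatory covariate has no value for participants or person-weeks without an illness onset, so the adjusted model as written cannot be fitted to the denominator that the same section defines. Anyone applying it literally must drop the illness-free or fill in values that depend on illness status, and then no longer estimates the stated rate ratio.

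How far the answer moves depends on the choice made: from about -1% (cases only), through 13% to 36% (filled-in values), to about 53% (odds ratio among the ill, a different estimand), against a true 50%. These values rest on the assumed epidemic shape and non-influenza illness risk, one season, and no propensity score or study-year term; the undefined covariate rests on none of them. Vaccination was fixed from the start in the simulation, so calendar time was not a confounder there. The 51% shows that the repaired term does no harm, not how much confounding it would remove.

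**What to change.** Replace the definition of calendar time with one that applies to every person-week at risk. For example: surveillance week, or its distance from the peak week, within study year, entered as a time-varying term in a Poisson model on weekly person-time. A Cox model on the calendar-time scale, stratified by study year, serves the same purpose.

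Keep weeks from onset to peak only if a test-negative analysis is intended. In that case label it separately as a sensitivity analysis that reports an odds ratio.

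The cost is one sentence in Data analysis of VE. Person-weeks of surveillance are already the denominator, so no new data are needed.
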